CLINICAL PROTOCOL COVER PAGE

**Protocol Title:** A Randomized Double-Blind, Placebo-Controlled Pilot Clinical Trial to Evaluate the Effect of Krill Oil on Knee Joint Pain

**Protocol Date:** June 12,, 2014

**Study Phase:** Pilot

**Study Design:** Randomized, double-blind, placebo controlled, 2-arm parallel

**Principal Investigator** [name].

Graduate School of Health & Sports Science, Juntendo University

[name]

# INTRODUCTION

Krill oil is an edible oil extracted from krill, a small red-colored crustacean found in the Antarctic Ocean [1]. Krill oil is rich in long-chain n-3 polyunsaturated fatty acids in the form of phospholipids [1].

Krill oil reduced tumor necrosis factor-α levels of lipopolysaccharide - stimulated peritoneal macrophages in obese Zucker rats [2]. The anti-inflammatory effect of krill oil was also observed in a rat model of dextran sulfate-induced experimental ulcerative colitis [3]. Krill oil consumption was shown to inhibit the progression of arthritis in an experimental mouse model of arthritis, in which the increase of inflammatory cytokines, IL-1 and IL-13, was suppressed [4]. Also, Deutsch et al. reported that krill oil administration mitigated the subjective symptoms of osteoarthritis as assessed by Western Ontario and McMaster Universities Osteoarthritis Index (WOMAC) and reduced C-reactive protein (CRP) levels in patients with cardiac disease, rheumatoid arthritis, or osteoarthritis with CRP levels greater than 1.0 mg/dL [5]. However, the effect of krill oil on mild knee pain has not yet been determined

The primary objective of this trial is to compare the efficacy of krill oil with a placebo in reducing the subjective symptoms of adults with mild knee pain.

# STUDY OBJECTIVES

To examine the effect of a 30 days (approximately 4 weeks) of krill oil administration on knee joint pain.

Primary outcomes**:**

- Japanese Knee Osteoarthritis Measure (JCOM)
- The Japanese Orthopedic Association knee rating score (JOA score)

Secondary outcomes**:**

- Blood and urine analysis
- Range of motion (ROM) of the knee

* ROM was deleted from the secondary outcome because of the difficulty to obtain the reliable data.

# STUDY DESIGN

This is a single-center, randomized, double-blind, placebo-controlled, 2-arm parallel group study. This study will consist of a 30 days administration period.

The planned sample size for this study is 50 healthy older adults, with 25 subjects randomized equally to each of the two-study arms in a double-blind manner.

| **Study Arm** | **Subject Number** |
| --- | --- |
| Krill Oil | N = 25 |
| Placebo | N = 25 |
| **Total** | **N = 50** |

In order to evaluate the goals of the study, assessments will be conducted at Visit 1 (Day 1) before administration of the test supplement (baseline), and Visit 3 (Day 31). Subject will visit or will be contacted by phone after 2 weeks of ingestion (Visit 2) in order to monitor adverse events and changes in concomitant medications as well as to foster compliance with the study dosing regimen.

The study will be conducted at a single site at Fukushima Orthopedic Clinic, Tochigi, Japan.

# SELECTION OF STUDY POPULATION

The target population for this study consists of 50 older men and women with mild knee joint pain.

Each subject will have to fulfill the inclusion criteria listed in Section 4.1. Subjects will not be included in the study if they meet any of the exclusion criteria listed in Section 4.2.

## Inclusion Criteria

1. Male or female adults with mild knee joint pain.
2. Subjects who have given voluntary, written, informed consent to participate in the study.

## Exclusion Criteria

1. Subjects who are breast feeding or pregnant or would be pregnant during the study.
2. Subjects who are under treatment with a biological agent, such as an antibody preparation, for knee pain.
3. Subjects with any major diseases of the cardiovascular, gastrointestinal, pulmonary or endocrine systems.
4. Subjects with active cancer (excluding basal cell carcinoma).
5. Subjects with neurological or significant psychiatric illnesses, including Parkinson's disease and bi-polar disorder.
6. Subjects with an allergy or sensitivity to the test supplement ingredient.
7. Subjects who are cognitively impaired and/or who are unable to give informed consent.
8. Subjects who are judged inadequate to enter the trial by Qualified Investigator.

## Concomitant Medications

Subjects who are currently taking any prescribed medications must agree to maintain their current method and dosing regimen during the course of the study.

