**Clinical reasons**

A subject may be withdrawn from the study if, in the opinion of the Qualified Investigator, it is not in the subject's best interest to continue. This includes but is not limited to adverse events related to the test supplement causing clinically significant illness, the need for prohibited concomitant medication or any participant who meets exclusion criteria during the trial. All serious adverse events will result in withdrawal from the trial. Participants who experience exacerbation of any current condition and require additional intervention or a change in their current intervention will be withdrawn from the trial.

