# STATISTICAL EVALUATION

## Determination of sample size

Sample size is set according to the report by Maki et al. [6], in which the administration of krill oil (2 g/d for 4 weeks) showed significant differences in the plasma EPA & DHA concentrations of 25 participants in the control and krill oil groups.

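### Non-prescription EPA/DHA products are unrestricted at entry and during the 30 days, so the between-arm contrast may be reduced by an unknown amount

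*Protocol*

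**What the plan says.** **Entry.** The Inclusion Criteria ask for consent and "Male or female adults with mild knee joint pain". Only one of the eight Exclusion Criteria is based on treatment: "Subjects who are under treatment with a biological agent, such as an antibody preparation, for knee pain". None concerns use of fish, krill or algal oil or of prescribed n-3, and there is no washout. The last criterion is discretionary: "Subjects who are judged inadequate to enter the trial by Qualified Investigator".

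**During the study.** The Concomitant Medications section (4.3 by its order after 4.2) consists of one sentence: "Subjects who are currently taking any prescribed medications must agree to maintain their current method and dosing regimen during the course of the study". Under Early Withdrawal, Clinical reasons, the grounds for withdrawal include "the need for prohibited concomitant medication or any participant who meets exclusion criteria during the trial", but no prohibited medication is listed or defined anywhere. The same section adds: "Participants who experience exacerbation of any current condition and require additional intervention or a change in their current intervention will be withdrawn from the trial".

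**Why EPA/DHA matters to this trial.** The Introduction states that "Krill oil is rich in long-chain n-3 polyunsaturated fatty acids in the form of phospholipids". The sample size rests on an earlier krill oil study that "showed significant differences in the plasma EPA & DHA concentrations of 25 participants in the control and krill oil groups". Plasma EPA and DHA are measured at Visits 1 and 3 and belong to the secondary outcome of blood and urine analysis.

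**The concern.** The test product is itself a food supplement of a kind that can be taken without a prescription. A concomitant rule limited to prescribed medication therefore misses the likeliest source of outside EPA/DHA. A subject can enter while taking fish oil, or begin it in week 2, and remain fully compliant with the text.

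Two things could then reduce the difference between arms. New n-3 use during the 30 days, above all in placebo subjects, would move the placebo arm toward the krill oil arm. Existing users given krill oil might respond less because they start from a raised level. Plasma EPA/DHA would be affected directly. JKOM and JOA would be affected if n-3 is what drives any benefit. With 25 subjects per arm there is little room to absorb such a loss.

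**Working it through.** **1. What the rules allow, case by case**

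| Situation | Rule in the protocol |
|---|---|
| Prescribed n-3, already taken at entry | Eligible; regimen to be kept unchanged (Concomitant Medications) |
| Prescribed n-3, started during the study | Not addressed, unless an exacerbation requires it (then withdrawal) |
| Non-prescription n-3, already taken at entry | No rule |
| Non-prescription n-3, started during the study | No rule, unless an exacerbation requires it (then withdrawal) |

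Nothing downstream catches the last two rows. The per-protocol population removes major violations, but n-3 use violates nothing written. The model for the primary outcomes adjusts for age, sex, weight, smoking and drinking, not for n-3 use or baseline EPA/DHA.

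**2. Which kinds of use shrink the contrast**

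The primary outcomes are analysed as change from baseline. Let Δ be the krill oil effect on change in a non-user, p the share of existing users in each arm, and r the fraction of Δ that users obtain.

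- Placebo, stable user: the outside product already acts at Visit 1, so the expected extra change is 0.
- Krill oil, existing user: the expected extra change is rΔ.
- Mean contrast = (1 − p)Δ + p·rΔ − 0 = Δ[1 − p(1 − r)].

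With r = 1 the contrast is Δ whatever p is, so stable use alone does not dilute. Dilution needs r < 1.

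For new use, let shares q₀ (placebo) and q₁ (krill oil) start a product and gain g₀ and g₁ from it. The contrast becomes Δ + q₁g₁ − q₀g₀. It falls when starting is commoner on placebo, or when added n-3 does less on top of krill oil. Equal and fully additive uptake would cancel.

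**3. Size on assumed inputs**

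The documents give neither p nor r. Assuming p = 10-30% and r = 0-50%:

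| p | r | 1 − p(1 − r) | Sample-size multiple 1/[1 − p(1 − r)]² |
|---|---|---|---|
| 0.10 | 0.5 | 0.95 | 1.11 |
| 0.10 | 0 | 0.90 | 1.23 |
| 0.30 | 0.5 | 0.85 | 1.38 |
| 0.30 | 0 | 0.70 | 2.04 |

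**4. What that means at 25 per arm**

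There is no planned power to reproduce: the sample size section gives no effect size, SD, alpha, power or dropout. As an illustration, assume two-sided alpha 0.05. The standardized effect with 80% power is d = (1.96 + 0.84) × √(2/25) = 0.79. Let f = p(1 − r) be the share of the contrast lost. Then power = Φ(0.792(1 − f)·√(25/2) − 1.96).

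| f | Effect | Power (normal) | Power (t test) |
|---|---|---|---|
| 0 | 0.79 | 80% | 78% |
| 5% | 0.75 | 76% | 74% |
| 10% | 0.71 | 71% | 70% |
| 20% | 0.63 | 61% | 59% |
| 30% | 0.55 | 50% | 49% |

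These figures show sensitivity to assumed inputs. They do not correct any number in the protocol.

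**The case against.** The strongest defence is that this is a pilot, and that testing krill oil on top of people's usual intake is a legitimate, broader question. Keeping prescribed regimens constant protects a change-from-baseline comparison. The investigator may refuse unsuitable candidates, concomitant therapies are reviewed at all three visits, and plasma EPA/DHA at Visits 1 and 3 could reveal users or off-protocol intake.

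Much of this stands, and it rules out several stronger readings:

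- **That any n-3 user on placebo dilutes the result.** A stable user carries the effect in the baseline score, so the change contrast is not reduced.
- **That the protocol names n-3 as the active component.** The Introduction says krill oil is rich in n-3 and credits the reported effects to krill oil. That fish oil would act on knee symptoms in the same way is an inference, hence the condition attached to JKOM and JOA.
- **That subjects are permitted to start a prescribed n-3.** The protocol does not address this; silence is not permission.
- **That chance imbalance of users between arms biases toward no effect.** It adds noise, not a systematic shift.

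What does not stand is that the safeguards close the gap. The discretionary exclusion contains no n-3 criterion, so it cannot secure consistent screening. The visit reviews and plasma levels would record use, but no action follows. A usual-intake design would still need usual intake to stay stable, and nothing asks that of non-prescription products. A statistical analysis plan could adjust for recorded use but could not prevent it.

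**Conclusion.** The point holds as a gap in eligibility and concomitant-product rules: non-prescription EPA/DHA is unrestricted at entry and during the 30 days, and the one reference to prohibited medication has no content. The consequence is a risk of a reduced contrast, not a demonstrated one. It depends on new use during the study, chiefly on placebo, or on a blunted response in existing users.

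For plasma EPA/DHA the mechanism is direct; for JKOM and JOA it also requires that n-3 drives the effect. If 10-30% of subjects are users and obtain 0-50% of the full effect, the mean effect is 95%-70% of its undiluted size. The lower figure combines the worst end of both assumed ranges. Confidence is moderate: the text is clear, the size is not. The change should be made because it is cheap, not because the loss is known to be large.

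**What to change.** 1. In 4.2, add an exclusion for current or recent use of EPA/DHA-containing products (fish, krill, algal or prescribed n-3), with the look-back window set by the sponsor. Prescribed users are then not enrolled, so no one is asked to stop a medicine.
2. In 4.3, add that subjects agree not to start a non-prescription EPA/DHA supplement before Visit 3.
3. Record such use at the concomitant-therapy reviews already scheduled at Visits 1, 2 and 3.
4. Reconcile the prohibited medication cited under Clinical reasons with 4.3, which prohibits nothing. The content of any such list is for the sponsor.

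The cost is one eligibility line, one sentence in 4.3 and a prompt at existing visits. A few candidates would be lost at screening, and the population would be slightly narrower.

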## Visit 2 – Week 2 (Day 14 ± 3)

Subjects will return to the clinic and the following will be discussed to reinforce product compliance:

- review of current conditions, concomitant therapies and adverse events
- compliance with test supplement

The Visit 2 can be performed via phone call.

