## Visit 3 – Week 8 End of Study (Day 31: 29 - 37)

Subjects will return to the clinic on day 31; Day 29– 37 will be possible according to the convenience of the subject.

Remaining test supplement in the original packaging will be returned.

Visit 3 assessments will include:

- concomitant therapies
- any adverse events
- Japanese Knee Osteoarthritis Measure (JCOM)
- The Japanese Orthopedic Association knee rating score (JOA score)
- Blood and Urine analysis
- Range of motion (ROM) of the knee
- Study diaries will be collected and reviewed.

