**8.2 Analytical Populations**

- The **Safety Population** will consist of all subjects who received any amount of either product, and on whom any post-randomization safety information is available.
- The **Per Protocol (PP) Population** “Per Protocol (PP) Population” consists of all subjects who consumed at least 80% of test or placebo doses do not have any major protocol violations and complete all study visits. Subject who has a compliance of <80% will be deleted from the further analysis.
  1. **Analysis Plan**

An effectiveness analysis based on the per protocol population will be performed. Continuous variables will be tested for normality and log-normality. Log-normally distributed variables will be analyzed in the logarithmic domain. Non-normal variables will be analyzed by appropriate non-parametric tests.

Missing values will be deleted in a pair-wise manner for the comparison, except in the structured questionnaires of JKOM (Q1 – 25) and JOA in which missing data will be deleted in a list-wise manner.

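### Self-bought painkillers are only partly controlled: Section 4.3 holds only existing prescribed drugs stable, and the withdrawal rules in 4.4 can remove subjects according to their symptom course

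*Protocol*

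**What the plan says.** The Concomitant Medications section (4.3) is one sentence: "Subjects who are currently taking any prescribed medications must agree to maintain their current method and dosing regimen during the course of the study". The only exclusion based on a drug concerns biological agents for knee pain (Exclusion Criteria). Non-prescription painkillers, oral or topical, are not mentioned anywhere.

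Use is monitored. Study Design gives Visit 2 the purpose, among others, of tracking "changes in concomitant medications as well as to foster compliance with the study dosing regimen". The Visit 2 section lists "review of current conditions, concomitant therapies and adverse events", and concomitant therapies are also reviewed at Visits 1 and 3.

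Early Withdrawal, Clinical reasons (4.4), contains two relevant rules:

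- A discretionary one: a subject may be withdrawn for reasons that include "the need for prohibited concomitant medication".
- A mandatory one: "Participants who experience exacerbation of any current condition and require additional intervention or a change in their current intervention will be withdrawn from the trial".

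Section 8.2 limits the per protocol set to subjects with at least 80% compliance who "do not have any major protocol violations and complete all study visits". On efficacy it states: "An effectiveness analysis based on the per protocol population will be performed". No other efficacy population is defined, and subjects who leave early are not replaced (Removal by Qualified Investigator). JKOM is completed by the subject and JOA by an orthopedist through interview, each at Visits 1 and 3 only.

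**The concern.** A subject who raises the dose of a prescribed painkiller breaks 4.3. A subject who buys the same drug over the counter does not. Both primary outcomes score knee symptoms, so pain relief from another source can enter the score.

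The consequence of such use is not settled either. The prohibited category has no list behind it. In the exacerbation sentence neither exacerbation nor intervention is defined, and self-medication is not addressed. One investigator may keep a subject who takes a painkiller for a worse knee, while another reading of the same sentence obliges withdrawal.

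If krill oil works, worsening should be more common on placebo. Subjects removed under the mandatory reading would then come more often from the placebo arm and from its poorer responders. That shrinks both the observed difference and the number analysed. These are rules for the conduct of the trial: an analysis plan can decide how to tabulate painkiller use, but it cannot recover a Visit 3 score that was never taken.

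**Working it through.** **Text check**

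| Situation | 4.3 | 4.4 | 8.2 |
| --- | --- | --- | --- |
| Existing prescribed painkiller increased | Breach | Mandatory withdrawal if an exacerbation required it | Possibly a major violation |
| Self-bought painkiller started or increased, no exacerbation | Not covered | Prohibited category undefined; exacerbation sentence does not apply | Not addressed |
| Self-bought painkiller for a worse knee | Not covered | Can be read as an added or changed intervention, hence withdrawal | Out of the set if withdrawn before Visit 3 |

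The second row is a gap. The third is an ambiguity, and its stricter reading selects on symptoms. If the use comes to light only at Visit 3, the protocol does not say whether the subject is scored and counts as having completed.

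**Size under assumptions**

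The protocol gives no SD, effect size, power or rate of painkiller use for the primary outcomes, so there is no figure of its own to reproduce. Only the 25 per arm comes from the protocol. Assumed inputs:

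- Change in score (higher is better) is N(0, 1) on placebo and N(0.8, 1) on krill oil, in SD units.
- A subject starts a painkiller if 0.5 × change + √0.75 × noise < c. The correlation between change and the tendency to use is therefore 0.5.
- c is set so that placebo use q is 10% or 30%.
- Relief from the painkiller is 0.3 to 0.5 SD.
- Two-sample t-test, two-sided 5%.

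Reference with no use: power 79.1%.

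*Use on krill oil*, Φ(c − 0.5 × 0.8):

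- q = 10%: c = −1.282, Φ(−1.682) = 4.63%.
- q = 30%: c = −0.524, Φ(−0.924) = 17.76%.

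*Users kept*, difference = 0.8 − (q − krill use) × relief:

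- q = 10%: 0.8 − 0.0537 × 0.3 = 0.784; with 0.5, 0.773.
- q = 30%: 0.8 − 0.1224 × 0.3 = 0.763; with 0.5, 0.739.

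*All users withdrawn.* Removing users raises each arm's mean by 0.5 × φ(threshold)/(1 − use), where the threshold is c on placebo and c − 0.4 on krill oil:

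- q = 10%: placebo +0.097, krill oil +0.051; difference 0.8 + 0.051 − 0.097 = 0.753 (three-decimal terms sum to 0.754). Expected numbers left are 25 × 0.90 = 22.5 and 25 × 0.9537 = 23.8.
- q = 30%: placebo +0.248, krill oil +0.158; difference 0.8 + 0.158 − 0.248 = 0.710. Expected numbers left are 25 × 0.70 = 17.5 and 25 × 0.8224 = 20.6.

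*Simulated power* (40,000 runs per case; ranges cover repeat runs, and for users kept also relief of 0.3 to 0.5 SD):

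| Handling | 10% placebo use | 30% placebo use |
| --- | --- | --- |
| Users kept | 78–79% | 77–79% |
| A quarter of users withdrawn (relief 0.4) | 77–78% | 75% |
| Half of users withdrawn (relief 0.4) | 76% | 71% |
| All users withdrawn | 73–74% | 61% |
| Same numbers lost at random | 76% | 66–67% |

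The last two rows separate the two sources of loss. At 30% use, 79 − 61 = 18 points are lost in all, and random loss alone accounts for 79 − 66 = 13 or 79 − 67 = 12 of them, about two thirds to nearly three quarters. At 10% use, random loss accounts for 79 − 76 = 3 of 5 to 6 points, about half. The remainder is shrinkage of the difference.

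**The case against.** The strongest reply is that 4.4 already does much of the work. Knee pain is the condition under study, so a new painkiller for a worse knee is naturally an added intervention, whether prescribed or bought. Therapies are reviewed at every visit. What is left unregulated is self-medication without exacerbation, in adults with mild pain over 30 days, in a trial labelled a pilot. This stands in part. A reader might infer that all self-bought painkiller use is unrestricted, and the documents do not support that. But the reply relies on the mandatory-withdrawal reading, which is the costlier of the two.

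It is also fair that the loss of about 18 points compares two extremes, every user kept against every user withdrawn. Case-by-case handling lies between them, and much of the loss is simply fewer subjects. A reader should not take that figure as an expected loss.

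Two stronger inferences also fail. One is a false positive: with equal use in both arms there is no bias, and if krill oil works the expected direction is dilution. The other is that a dose taken just before scoring must distort the score, so that a washout is needed. The protocol states no recall period for either instrument, so neither the acute effect nor a particular interval can be derived from it.

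**Conclusion.** The point holds as a limited defect of the conduct rules. Section 4.3 leaves self-bought painkillers outside the stable-regimen rule except where the exacerbation sentence reaches them. The prohibited category has no content. The mandatory sentence can remove subjects from the only efficacy set in a way linked to how their knees progress.

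The likely consequence is modest dilution and loss of power, of unknown size. Under the assumed inputs, kept use costs about 0 to 2 points. Withdrawal costs more, up to about 18 points as an upper bound at 30% placebo use. The assumptions are the 0.8 SD effect, the use rates, the correlation of 0.5 and the relief of 0.3 to 0.5 SD; none comes from the protocol. The change is worth making because it is cheap, not because the trial would be invalid without it.

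**What to change.** - **4.3:** Extend the stable-regimen rule to non-prescription painkillers, oral and topical. Ask subjects to avoid new or increased use where tolerable. Record product, dose and date in the existing diary and at the existing visit reviews.
- **4.4:** Define the prohibited category or delete it. Amend the exacerbation sentence itself, so that starting or increasing a painkiller for knee pain does not by itself cause withdrawal and such subjects still attend Visit 3 and are scored. A separate statement placed beside an unchanged mandatory sentence would leave the conflict in place.
- **8.2:** State that such use alone is not a major protocol violation. Otherwise the wider rule in 4.3 could remove the same subjects by another route.

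A painkiller-free interval before scoring is not recommended. It would conflict with keeping a stable regimen, and it could not be instructed in advance, because consent, randomization and baseline scoring all fall under Visit 1.

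The cost is a few sentences and one diary entry, with no added visits or subjects. The downside is a slight diary burden, and some painkiller use will remain in the scores analysed.
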